## Abstract

**Introduction:**

Reducing length of hospital stay for stroke survivors often creates a shift in the responsibility of care towards informal carers. Adjustment to the caregiving process is experienced by many carers as overwhelming, complex and demanding and can have a detrimental impact on mental and physical health and well-being. National policy guidelines recommend that carers’ needs are considered and addressed; despite this, few interventions have been developed and empirically evaluated. We developed a biopsychosocial intervention in collaboration with carers of stroke survivors. Our aim is to determine whether the intervention can be delivered in a group setting and evaluated using a randomised controlled trial (RCT).

**Methods and analysis:**

Feasibility RCT and nested qualitative interview study. We aim to recruit up to 40 stroke carers within 1 year of the stroke onset. Carers are randomised to usual care or usual care plus biopsychosocial intervention. Each intervention group will consist of five stroke carers. The intervention will focus on: psychoeducation, psychological adjustment to stroke, strategies for reducing unwanted negative thoughts and emotions and problem-solving strategies. The main outcome is the feasibility of conducting an RCT. Carer outcomes at 6 months include: anxiety and depression, quality of life and carer strain. Data are also collected from stroke survivors at baseline and 6 months including: level of disability, anxiety and depression, and quality of life.

**Ethics and dissemination:**

Favourable ethical opinion was provided by East Midlands – Nottingham2 Research Ethics Committee (14/EMI/1264). This study will determine whether delivery of the biopsychosocial intervention is feasible and acceptable to stroke carers within a group format. It will also determine whether it is feasible to evaluate the effects of the biopsychosocial intervention in an RCT. We will disseminate our findings through peer-reviewed publications and presentations at national and international conferences.

**Trial registration number:**

ISRCTN15643456; Pre-results.

Strengths and limitations of this studyEnhancing the well-being of carers is a national priority. However, few interventions for carers have been developed or evaluated.This is a pragmatic trial conducted in a real-world setting. The intervention content is based on the findings from the literature, developmental work with carers of stroke survivors and stroke rehabilitation experts.This feasibility study will be conducted in a single site only.The intervention focuses only on the initial stages of carer support (up to 1 year poststroke onset). Significant problems may develop for carers at later stages that need to be identified and referred for more intensive/specialist support.

## Introduction

### Background and rationale

A carer has been defined as ‘a person of any age who provides unpaid help and support to a relative, friend or neighbour who cannot manage to live independently without the carer’s help due to frailty, illness, disability or addiction’.^1^ Carers play a vital role in the early rehabilitation process and long-term management of the stroke survivor.^2^ Carers deal with a range of care needs and demands including mobility, self-care, communication difficulties as well as cognitive impairment, mood and personality changes in the stroke survivor.^3^

The latest figures from the Sentinel Stroke National Audit in England, Wales and Northern Ireland show that the median length of inpatient stay is between 7 and 8 days; however, just under one-third of stroke survivors who were discharged requiring help with daily activities received assistance from informal carers.^4^ This demonstrates that increasingly shorter hospital stays coincide with an earlier transfer of care to informal carers in the community. The Care Act 2014 has placed a responsibility on local authorities in England to consider the well-being of carers as being of equal importance to the well-being of the people they care for.^5^ The importance of providing support and intervention to carers has also been emphasised in national stroke guidelines.^6 7^ Consequently, it is becoming more urgent to develop appropriate and effective interventions to meet the specific needs of carers of stroke survivors.

A growing number of people are unexpectedly finding themselves in the caregiving role. Although it can be a positive and rewarding role,^8^ the increased demands associated with informal caring can place carers at elevated risk of poorer mental and physical health, accompanied by reduced opportunity for paid employment and social interaction and activity.^3^ An estimate of the psychosocial impact that might be associated with stroke care, drawn from a survey of carers,^9^ shows that carers may experience: anxiety (79%), frustration (84%), sleeping disturbances (60%), depression (56%) and stress (57%). Deterioration in the health and well-being of the carer has important implications on the outcomes of stroke survivors including: poorer rehabilitation outcomes; reduced quality of life; heightened levels of depression; greater risk of mortality; poorer treatment adherence; and increased likelihood of being placed into institutional care, which has important cost implications for the NHS, social care services, the stroke survivor and their family.

An increased focus on the needs of stroke carers has led to a spate of recent systematic reviews including quantitative and interventional studies,^10–13^ qualitative research^8 14^ and economic evidence.^15^ However, the results are equivocal and limited. Thus, there is no clear and robust evidence regarding the most effective and cost-effective interventions for stroke carers. This lack of evidence is not due to the lack of research in this field^11^; interventions directed at both stroke survivors and carers form the largest body of research and have predominantly focused on examining new models of service delivery,^16^ such as care-giver training, the stroke family support worker^17 18^ and multidisciplinary hospital and community stroke teams. These interventions however have predominantly focused on the stroke survivors’ needs rather than the carers’ needs,^19^ and thus the needs of carers have largely been neglected. The few interventions to date that have been developed specifically for carers include education and information,^20^ skills training^21^ and social support.^22^ Such interventions however have produced inconclusive findings, arguably because such interventions are failing to address and meet the specific needs of carers. Forster *et al*^23^ evaluated a structured caregiver training programme delivered in hospital by multidisciplinary teams from stroke units. There was no difference between the intervention and usual care, and they concluded that the immediate period after stroke might not be the best time to deliver such a programme.

Given the high prevalence of psychological morbidity within the stroke carer population, there is likely to be a high demand for psychologically informed interventions targeted at informal carers of stroke survivors beyond the initial period of hospitalisation. Although evidence-based treatments for psychological difficulties exist, the associated costs and expenses of service delivery are high, with demand for treatment exceeding service capacity, resulting in long waiting lists^24^ and limited access.^25^ There are other barriers experienced by carers wishing to pursue and access mental health services.^26^ These barriers include a lack of attention by health professionals of the difficulties associated with the caregiving role and that general practitioners are often more likely to offer practical rather than psychological support. Together these reasons make it increasingly difficult for informal carers to access evidence-based psychologically informed interventions.

The biopsychosocial model of health and illness, as proposed by Engel,^27^ suggests that psychobiological vulnerability is influenced by an interaction of biological (physical health), psychological (thoughts, emotions and behaviours) and social (relationships and roles) factors. The model emphasises the need for interventions to focus on both symptom reduction and on relapse prevention.^28^ Psychological models such as cognitive–behavioural and interpersonal therapy have been deemed too fragmented and reductionist,^29^ given that they do not integrate the biological and psychological factors, as well as social, environmental and stress factors that are known to interfere with psychological functioning.

There have been movements towards the use of biopsychosocial interventions for the treatment of psychological difficulties among the general population. However, evidence suggests that significant adaptations to such interventions are required prior to application to different clinical populations. Indeed, mental health services for carers have been criticised for not being tailored to address the unique and specific difficulties experienced by stroke carers.^30 31^ Such difficulties can include having to manage the physical and cognitive impairment and behavioural difficulties the stroke survivor may be presenting with.^32 33^ There is growing recognition of the importance of understanding carer’s experiences when dealing with health resources and healthcare policy.^34^ A systematic review of psychosocial interventions for stroke carers concluded that more randomised controlled trials (RCTs) of psychoeducation programmes are needed.^12^

Considering this recommendation in the context of the wider literature on stroke carers, we developed a new biopsychosocial intervention specifically targeted at informal carers of stroke survivors. The intervention was developed collaboratively with stroke carers and designed to be delivered in a group format to offer participants the opportunity to meet and interact with people and listen to how others have coped. Delivering the intervention in a group format is also likely to be more time and cost efficient, which would be important given the current demand for psychological therapies.

This study is examining the feasibility of conducting a RCT to examine the effectiveness and acceptability of this group biopsychosocial intervention for stroke carers in the first-year poststroke.

### Research aim and objectives

The ultimate aim of this study is to evaluate whether a biopsychosocial intervention can improve psychological outcomes in carers of stroke survivors (in the 1-year poststroke period). However, we are not able to complete a definitive, powered trial until we have collected further information to inform the design of such a study. The purpose of this feasibility trial is to explore whether the biopsychosocial intervention for carers of stroke survivors is feasible and acceptable and to estimate the parameters for conducting a fully powered trial.

#### Primary objective

The primary objective of this feasibility trial is to evaluate whether it is feasible to deliver a biopsychosocial intervention to carers of stroke survivors as part of an RCT.

#### Secondary objectives

This feasibility RCT will test the integrity of the study protocol, such as the methods of data collection, randomisation procedures and the masking of independent assessors. This feasibility study will answer the necessary questions to inform a definitive multicentre trial that include:Can we identify participants willing to be randomised?Can we deliver the intervention as planned?Is the intervention acceptable to participants?Can we retain participants in the study?What are the most relevant outcome measures?What is the consent rate?

## Methods and analysis

### Study design and setting

This is a single-centre feasibility RCT with nested qualitative interview study. The RCT is a parallel group, two-arm trial with a 1:1 allocation ratio of biopsychosocial intervention:usual care control.

### Participants

Participants are carers of people who have had a stroke (stroke survivors). Our definition of a carer is a family member or friend who is/will be providing support for a stroke survivor who would not be able to manage without their help due to their condition. Carers will be recruited along with stroke survivors from stroke units at a university hospital, community stroke services and third sector stroke clubs and support groups. However, only the carer will receive the intervention; we will recruit the stroke survivor because we also aim to collect baseline and follow-up data from them.

The inclusion criteria are as follows:

Stroke carersaged 18 years or overcarer of a person with a confirmed diagnosis of stroke within 1 year of stroke onsetcapacity to provide informed consentwilling to attend a 6-week group intervention programme.

Stroke survivorsaged 18 years or overconfirmed diagnosis of strokewithin 1 year of stroke onsetcapacity to provide informed consent or consultee opinion that the person would wish to participate.

The exclusion criteria are as follows:

Stroke carersunable to speak Englishengaged in other research involving biopsychosocial/psychological interventionspeople with visual (blindness) or auditory (deafness) impairments that would preclude them from participating in the therapy sessions.

Stroke survivorsunable to speak Englishpeople engaged in other research involving biopsychosocial/psychological interventions.

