**Intervention group: biopsychosocial intervention, plus usual care**
Carers randomised to the intervention group will receive the biopsychosocial intervention, in addition to usual care. The stroke carers randomised to receive the intervention will receive a 2-hour session once a week for 6 weeks. The time point at which the intervention will start will be agreed with the carer, in conjunction with other carers likely to be part of that group. This will occur when the stroke survivor they care for has been discharged from hospital, up to 1 year poststroke. We will aim to deliver the intervention to groups of approximately five people. However, in the event that it is not possible to coordinate sufficient people, or where carers are unable to attend the group sessions, we will deliver the intervention on a one-to-one basis or in smaller groups. We will record this as part of our feasibility. The intervention will be delivered at a suitable venue, with sufficient space and access for carer group members. The intervention sessions will be facilitated by a research psychologist who has received training in the principles of biopsychosocial theory as well as specific training from members of the research team responsible for the development of the intervention. Clinical supervision and debriefing sessions will be provided by an experienced community mental health nurse with significant community stroke team experience and/or a clinical psychologist. Each session will last approximately 2 hours and will include a 15 min tea/coffee break that will allow participants to interact more informally with one another, and the session will conclude with a 15 min relaxation exercise. We anticipate that in the definitive trial, the intervention could be delivered by assistant psychologists with supervision from clinical psychologists.The intervention programme is focused on adjustment to stroke, provision of psychoeducation and psychological support. The group programme is based on the principles of the biopsychosocial model. The sessions are designed to teach individuals to identify and use skills to reduce current and future distress, thus aiding coping and adjustment to the impact of stroke and their role as a carer. The sessions are also intended to increase awareness of the role of thoughts, emotions and behaviours and their influence on each other. By practising problem-solving and stress-management strategies, it is hoped that carers will experience fewer difficulties with their mood in the future.For each session, there will be a presentation containing information about a topic and exercises to aid discussion. Sessions will be presented on Microsoft PowerPoint, and all participants will receive either electronic or paper copies of the slides as appropriate, accompanied by the exercise and an in-between session task. The topics will cover, for example, an introduction to stroke and caring, adjustment and mood, how to handle negative emotions and thoughts, dealing with problems and a well-being relapse prevention plan (which provides a set of coping mechanisms to deal with individual triggers of the stress response in relation to the role as stroke carers to encourage and foster positive mental health). The content of these sessions was informed by the findings of earlier work described above. Relaxation exercises at the end of each session will allow participants to feel calm and relaxed before finishing their session and will also be an effective tool for them to use outside of the session when experiencing high levels of anxiety or distress. Between session tasks will be set to encourage participants to practice exercises from the sessions in their own time. Participants who are identified to be experiencing significant issues that are out of the scope of the intervention will be referred onto the appropriate specialist service, subject to their consent.

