#### Tolerability

Proportion of carers who withdraw or decline intervention. Record of interventions declined and why.

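### Willingness to attend a group is an entry criterion, so the trial screens out carers who reject the format whose acceptability it is meant to estimate

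*Protocol article*

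**What the plan says.** The carer inclusion criteria (Participants) require willingness "to attend a 6-week group intervention programme".

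The abstract (Ethics and dissemination) says the study will determine "whether delivery of the biopsychosocial intervention is feasible and acceptable to stroke carers within a group format". Secondary objectives asks "Is the intervention acceptable to participants" and "What is the consent rate". Outcomes builds the main feasibility outcome from several parts. The realism of the eligibility criteria is one, and the feasibility and acceptability of delivering the intervention is another.

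The description of the intervention arm allows other formats. If too few carers can be brought together, or "where carers are unable to attend the group sessions, we will deliver the intervention on a one-to-one basis or in smaller groups". It adds: "We will record this as part of our feasibility".

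The measures that bear on acceptability are:
- recruitment, eligibility and consent among carers screened, and sessions attended (Acceptability of the study design);
- the proportion completing (Feasibility of completing the intervention);
- "Proportion of carers who withdraw or decline intervention", with reasons recorded (Tolerability);
- interviews held after the final outcome assessment (Feedback interviews).

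**The concern.** The criterion selects on an attribute that the trial sets out to estimate. A carer who tells recruiting staff that a group is out of the question fails an inclusion criterion and leaves before consent is sought. That carer is not among those who attend, complete, withdraw from or decline the intervention, and is not interviewed. The refusal appears, if at all, as ineligibility.

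Planners of the definitive trial would act differently on a finding that few carers are eligible than on a finding that many refuse groups. The first points to the entry criteria or the recruitment sources, the second to the intervention format. Outcomes lists eligibility and acceptability as separate components, and the criterion moves refusals from the second to the first.

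There is also a practical problem of classification. A carer who cannot come to a group may be turned away if this is known at screening, but may receive one-to-one delivery if it emerges after randomisation. Enrolment is shared between Clinical Research Network staff and the research team, so such carers may be classed inconsistently.

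**Working it through.** The document states no consent, eligibility or acceptability rate, so there is no figure of the plan's to reproduce. What can be checked is how each rate responds to the way group-refusers are classed.

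**Inputs**
- C = 40 consenting carers, the recruitment target (Sample size, recruitment strategy, randomisation and blinding).
- D = carers who decline for other reasons. Assumed: 20, 40 or 80.
- G = carers who meet every other criterion but reject the group format. Assumed: 10, 20 or 40.
- I = carers ineligible for other reasons. Assumed: 20.

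**Formulas**
- Consent over eligible carers, criterion applied as written: C / (C + D).
- Consent over carers meeting all other criteria: C / (C + D + G).
- Consent over screened carers: C / (C + D + G + I). This is the same whether G is called ineligible or declining.

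With u = G / (C + D + G), the first rate is the second multiplied by 1 / (1 − u).

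**Results**

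| D | G | Over eligible, as written | Over all otherwise eligible | Difference (points) |
|---|---|---|---|---|
| 20 | 10 | 40/60 = 66.7% | 40/70 = 57.1% | 9.5 |
| 20 | 20 | 66.7% | 40/80 = 50.0% | 16.7 |
| 20 | 40 | 66.7% | 40/100 = 40.0% | 26.7 |
| 40 | 10 | 40/80 = 50.0% | 40/90 = 44.4% | 5.6 |
| 40 | 20 | 50.0% | 40/100 = 40.0% | 10.0 |
| 40 | 40 | 50.0% | 40/120 = 33.3% | 16.7 |
| 80 | 10 | 40/120 = 33.3% | 40/130 = 30.8% | 2.6 |
| 80 | 20 | 33.3% | 40/140 = 28.6% | 4.8 |
| 80 | 40 | 33.3% | 40/160 = 25.0% | 8.3 |

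Consent over screened carers, for D = 40 and G = 20, is 40 / (40 + 40 + 20 + 20) = 33.3% under either classification.

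**Attendance.** Suppose 80% of willing carers attend (assumed), and a fraction u of otherwise eligible carers reject groups. Attendance over all otherwise eligible carers is then 0.80 × (1 − u). This gives 72% at u = 10%, 64% at 20%, 56% at 30% and 48% at 40%. The trial as written would report 80% in every case.

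**Criterion and delivery route side by side.** Participants speaks of willingness. The intervention section speaks of inability to attend, or of too few carers to form a group. A carer can be willing at entry and unable later, and both sections can then be followed. They pull apart for a carer who would not or could not join a group but could use the one-to-one route. The entry criterion can exclude that carer, while the intervention section has a place for one in the same position.

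**The case against.** The strongest reply is that nothing is hidden. The reporting described under Acceptability of the study design starts from carers screened, and on that base the consent figure does not depend on how refusers are classed. Because the realism of the eligibility criteria is itself under test, a heavy loss on willingness would show as a low eligible proportion. A reader might infer that the reported consent rate will be overstated. The document does not support that as a fact, because it fixes no denominator for the consent rate. The bias arises only if the rate is taken over eligible carers.

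A reader might also infer that the entry criterion and the one-to-one route contradict each other. That is too strong, since being willing and being unable are different things. Failures of the group format among carers who enter are to be recorded as feasibility information.

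Other fair points are that Tolerability states no denominator and does ask for reasons, that the acceptability objective speaks of participants, and that coding of screening reasons is detail an article may leave to the full protocol. Requiring willingness to attend is also a legitimate design choice. Admitting many carers who reject groups would weaken the test of group delivery in about 20 intervention carers.

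What survives is narrower. Applied as written, the criterion keeps group-refusers out of the attendance, completion and decline measures whatever denominator is used for consent. A lower eligible proportion does not by itself show that the format was the reason.

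**Conclusion.** The entry criterion screens on something the trial is meant to estimate. The attendance, completion and decline rates will describe carers who had already said they would join a group. Any consent rate over eligible carers is biased upwards by the factor 1 / (1 − u), and the rate over screened carers is unaffected. The document gives no value for u. The 2.6 to 26.7 points for consent, and the fall from 80% to between 72% and 48% for attendance, rest wholly on the assumed counts and show only what could happen.

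The entry criterion and the delivery route are in tension and must be reconciled. The planned 40 dyads are not affected. The change is worth making because it alters what the trial can conclude about acceptability of the group format, at almost no cost.

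**What to change.** 1. Give carers who meet all other criteria but will not or cannot attend a group their own screening category, such as *otherwise eligible, declined – group format*, with the reason recorded. Count them as non-acceptance of the group format.
2. Report the consent rate over all screened carers and over carers meeting all other criteria. State the denominator each time, including for the decline rate.
3. Reword the carer criterion under Participants so that it agrees with the delivery formats in the intervention section. If the reconciled wording lets a carer who rejects groups enter by the one-to-one route, count that carer as consenting to the trial but not as accepting the group format.

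Removing the criterion altogether is a separate and debatable design choice, and steps 1 and 2 do not depend on it.

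The cost is an amendment to one criterion, one extra screening-log code, and less favourable reported consent and acceptability rates. Recruitment opened on 1 November 2015, so refusals logged before the change without a reason may not be recoverable. The report should say from when the code was used.
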